### Trial design

The MATCH trial is designed as a multicentre, open-label, parallel-group, phase 2, RCT to compare autologous macrophage therapy with standard medical care in patients with compensated cirrhosis. Randomisation will be performed with a 1:1 allocation ratio and the primary outcome is the baseline to 90-day change in Model for End-Stage Liver Disease (MELD) score. Figure 1 provides an overview of trial pathway following randomisation to the respective arms. Initially, the proposed trial was designed to administer three infusions to those randomised to the treatment arm. It became apparent that it would not be acceptable or feasible to continue with three infusions due to the onerous commitment required of participants and the challenge to complete the trial within the proposed time frame. Therefore, as a pragmatic approach, and in line with the phase 1 study, it was decided that a single infusion protocol should be adopted to simplify the participant journey and ensure adequate recruitment. This was agreed with the trial steering committee (TSC), sponsor and data monitoring committee (DMC).

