### Interventions

Participants who are randomised to the treatment arm will receive an infusion of the maximum achieved dose up to 1×10^9^ (day 0). The apheresis product will be collected under the terms of the Human Tissue (Quality and Safety for Human Application) Regulations 2007 No. 1523 enacting the requirements of the EU Tissues and cells Directive (2004/2023) and associated Commission Directives at the Apheresis Unit (Royal Infirmary of Edinburgh, Edinburgh, UK). CD14+ monocytes will be isolated, and the macrophage cell product will be manufactured as previously described,^25^ in compliance with GMP regulations under the terms of the SNBTS MIA (IMP) licence at the SNBTS Cell Therapy Facility (Scottish Centre for Regenerative Medicine, Edinburgh, UK).

Each patient will be monitored closely during the infusion to identify potential hypersensitivity reactions and 4 hours postinfusion bloods to monitor for any evidence of macrophage activation syndrom. A total of 28 participants will be randomised to standard medical care and 28 to receive the cell infusion, allowing for original estimate of 5 dropouts from each arm. Additional safety data will be collected for the first infusion only for the first three patients randomised to the treatment arm. If it has not been possible to achieve 1×10^9^ macrophages, then the participants will be infused with the quantity obtained, with minimum concentration being 1.25×10^8^ cells. This minimum cell concentration was derived from previous validation work and is stipulated as part of the product release criteria as designated by the MHRA.

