### Sample size/power calculation

To detect a difference in the baseline to 90-day change in MELD score of 1 SD using a two-sided, two-sample test with a 5% level of significance, a sample size of 23 per group to detect the same level of difference with 90% power is required. All analyses will be carried out on an intention to treat basis, retaining participants in their randomised treatment groups irrespective of the treatment received. Adverse event (AE) data will be presented by treatment received.

The number of participants who do not adhere to the protocol is expected to be low. All protocol violations and ineligible participants will be recorded.

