### Statistical analysis plan

The baseline to 90-day change in MELD score will be compared in the two treatment arms using a two-sample t-test or non-parametric equivalent as appropriate. MELD scores calculated for each participant throughout the trial will be used to calculate an area under the curve (AUC) and this will be compared across the groups using a two-sample t-test or non-parametric equivalent as appropriate. In the event of varying durations in the trial follow-up, the average AUC per month will be used so that all participants have a comparable measurement.

Changes in secondary outcome measures (ELF score liver stiffness, CLDQ score, transplant-free survival, number of clinical events, UKELD score, blood parameters (bilirubin, albumin, ALT, INR)) over the 1-year study period will be presented graphically by dose. Similarly, these results will used to calculate an AUC for each participant and will be compared across the groups using a two-sample t-test or non-parametric equivalent as appropriate.

The only planned subgroup analysis is to present the primary outcome by disease aetiology (ALD, NAFLD, other). Primary data analysis will be conducted on participants who receive a single infusion versus control; the primary analysis will then be repeated to include those subjects who receive more than one infusion (three individuals). There are no plans for an interim analysis.

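### The primary analysis selects the active arm by infusions received, which conflicts with the plan's intention-to-treat rule and leaves the primary analysis set undefined

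*Protocol article*

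**What the plan says.** The protocol article gives two rules for who is analysed.

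- Sample size/power calculation: "All analyses will be carried out on an intention to treat basis, retaining participants in their randomised treatment groups irrespective of the treatment received". The only exception named there is safety: "Adverse event (AE) data will be presented by treatment received".
- Statistical analysis plan: "Primary data analysis will be conducted on participants who receive a single infusion versus control". It adds that "the primary analysis will then be repeated to include those subjects who receive more than one infusion (three individuals").

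The background is in Trial design: "Initially, the proposed trial was designed to administer three infusions to those randomised to the treatment arm". This was later cut to one infusion because three proved too demanding for participants and too slow for the trial's time frame. The same section says that "the primary outcome is the baseline to 90-day change in Model for End-Stage Liver Disease (MELD) score". Under Interventions, "A total of 28 participants will be randomised to standard medical care and 28 to receive the cell infusion", with five dropouts allowed for in each arm.

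**The concern.** The first rule groups participants by what they were allocated. The second groups the active arm by what they received and applies no matching condition to the controls. The subject is the primary endpoint, and the article states both rules itself, so this is not a detail left to a fuller plan.

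Two things are at stake. First, any exclusion that depends on events after randomisation, in one arm only, gives up the protection of randomisation. Second, with 56 participants and staff who know the allocation (Blinding), an ambiguous primary set could be settled after results are seen, and either choice could be defended from the text.

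**Working it through.** **Who is in which analysis**

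| Participants | Intention-to-treat rule | Primary run, literal | Repeat run, literal |
|---|---|---|---|
| Controls, either period | In | In | In |
| Cells, one infusion | In | In | In |
| Cells, more than one infusion (3) | In | Out | In |
| Cells, never infused | In | Out | Out |

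The third row is a conflict on any reading. The fourth is a conflict only if the wording is taken literally.

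The filter uses infusions received, not the date of randomisation or the protocol version. Someone allocated to three infusions who stopped after one would stay in the primary run, while those who went on are removed. Controls randomised in the three-infusion period stay in, so the comparison is not fully concurrent.

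**Can a participant be randomised to cells and not infused?** The document shows how it could happen. Randomisation follows confirmation of eligibility. Table 1 puts apheresis and then infusion after that, with infusion about 7 to 10 days after apheresis. Product release also has a floor: "with minimum concentration being 1.25×10^8^ cells". No number or rate of non-infusion is given.

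**The plan's own figure.** For a 1 SD difference, two-sided 5% and 90% power, the noncentral t calculation gives 23 per group (power 91.2% at 23, 89.97% at 22). This agrees with the stated 23, and 28 − 5 = 23. The sample size is not in question.

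**Illustration of bias from leaving out never-infused participants.** Assumptions: no true effect; 28 per arm; no other missing data; common SD of 1. Suppose k active-arm participants are excluded and their mean MELD change is D SD worse than that of the remaining 28 − k. With no effect, the whole active arm has the same expected mean as control. The remaining participants therefore look better than control by

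shift = k × D / 28.

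The rejection rate comes from the noncentral t with 54 − k degrees of freedom and noncentrality shift / √(1/(28 − k) + 1/28).

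| k excluded | D (SD) | Shift (SD) | Two-sided type I error |
|---|---|---|---|
| 1 | 0.5 | 0.5/28 = 0.018 | 5.05% |
| 3 | 0.5 | 1.5/28 = 0.054 | 5.4% |
| 3 | 1 | 3/28 = 0.107 | 6.7% |
| 5 | 0.5 | 2.5/28 = 0.089 | 6.1% |
| 5 | 1 | 5/28 = 0.179 | 9.5% |

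Both k and D are assumed. The upper k equals the plan's dropout allowance per arm, but the plan does not say that dropouts are people who were not infused.

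**The case against.** The best defence is that the sentence was written to separate two regimens. It contrasts one infusion with more than one, the reason is given under Trial design, and it says nothing about participants with none. The same section opens by comparing the two treatment arms, and the intention-to-treat rule already covers people who were not treated. On that reading the repeat run is the full intention-to-treat analysis. This is a fair reading, and it means the loss of never-infused participants is a possibility and not a stated exclusion. It does not remove the conflict: the run labelled primary still omits three randomised participants because of the treatment they received.

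Three stronger conclusions are tempting, and the document does not support them.

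- A reader might infer that neither planned analysis is by intention to treat. That holds only on the literal reading.
- A reader might infer that the exclusions favour treatment. The only exclusion actually stated is of people who completed more than one infusion. They tolerated a heavier schedule and received more treatment, so removing them could equally work against the active arm. The favourable direction applies only to never-infused participants, and only if they do worse.
- A reader might infer that the trial becomes underpowered. If the three are among the 28, and none of them is among the five dropouts, 20 v 23 gives 89.1%, against 91.2% for 23 v 23. That loss is about two points, and the article does not say whether the three are among the 28.

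It is also true that some participants who withdraw before infusion will have no 90-day MELD score and are already covered by the dropout allowance. Redefining the set does not recover their outcomes. It matters for those who are not infused but are still followed.

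**Conclusion.** The point stands as a contradiction over the primary analysis set. On any reading, three known participants are left out of the primary run against the plan's own rule, while the controls are unrestricted. On the literal reading, never-infused participants are also missing from both runs.

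The effect of dropping the three has unknown direction. The effect of dropping never-infused participants ranges in the illustration from negligible (5.05%) to a near doubling of the nominal 5% error (9.5%). Those figures rest on assumed numbers and an assumed prognosis, and are not an estimate for this trial. The case for correction rests on the conflict in the text and on the need to settle the primary set before outcomes are examined.

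**What to change.** Replace the sentence on the primary data analysis with one stating that the primary analysis includes all randomised participants in the arm to which they were allocated, whatever number of infusions they received (0, 1 or more).

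State how the 90-day time point is fixed for participants who are never infused. Table 1 ties Day 0 in the treatment group to the infusion visit, so these participants have no Day 90 as it stands. Count theirs from a stated origin common to both arms.

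Keep the interest in the single-infusion regimen as a labelled sensitivity analysis. Restrict both arms to participants randomised after the single-infusion change took effect, so that the comparison stays randomised and concurrent.

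The cost is a change of wording plus the time-origin definition. The price in the estimate is slight dilution from any non-infused participants and the inclusion of three people treated under the earlier regimen.

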### Data monitoring

The trial will be coordinated by a project management group, consisting of the grant holders (chief investigator and principal investigator in Edinburgh), a trial manager and coordinating nurse.

The trial manager will oversee the study and will be accountable to the chief investigator. The trial manager, or an authorised member of the research team, will be responsible for checking the CRFs for completeness, plausibility and consistency. Any queries will be resolved by the Investigator or delegated member of the trial team. A Delegation log will be prepared detailing the responsibilities of each member of staff working on the trial.

### Safety assessments

The investigator is responsible for the detection and documentation of events meeting the criteria and definitions detailed within the protocol (available on request). Full details of contraindications and side effects that have been reported following administration of the IMP can be found in the relevant investigator’s brochure.

Participants will be instructed to contact their Investigator at any time after consenting to join the trial if any symptoms develop. All AEs that occur after joining the trial must be reported in detail in the CRF or AE form. In the case of an AE, the investigator should initiate the appropriate treatment according to their medical judgement. Any AE events still present on day 360 will be confirmed and recorded as ‘ongoing’ in the CRF. If appropriate, these should be handed over to the participants’ general practitioner or direct care team.

The ACCORD Research Governance and QA Office is responsible for pharmacovigilance reporting on behalf of the cosponsors (University of Edinburgh and NHS Lothian).

The ACCORD Research Governance and QA Office has a legal responsibility to notify the regulatory competent authority and relevant ethics committee (Research Ethics Committee (REC) that approved the trial). Fatal or life threatening Suspected Unexpected Serious Adverse Reactions (SUSARs) will be reported no later than seven calendar days and all other SUSARs will be reported no later than 15 calendar days after ACCORD is first aware of the reaction.

ACCORD will inform investigators at participating sites of all SUSARs and any other arising safety information.

An annual safety report/development safety update Report will be submitted, by ACCORD, to the regulatory authorities and RECs listing all SARs and SUSARs.

### Monitoring and oversight

An ACCORD clinical trials monitor, or an appointed monitor will visit the investigator site prior to the start of the study and during the course of the study if required, in accordance with the monitoring plan if required. Risk assessment will determine if audit, by the ACCORD QA group, is required. Details will be captured in an audit plan.

## Discussion

MATCH is an RCT designed to identify whether there is a measurable improvement in MELD score and also in relevant secondary clinical outcomes, HRQoL and non-invasive biomarkers following autologous macrophage therapy. It builds on the safety and feasibility assessment of the earlier phase I trial. Recent Food and Drug Administration (FDA) guidance on development of treatments for cirrhosis has indicated there are no acceptable surrogate endpoints (eg, histological improvement) so our focus in this study is on clinically meaningful assessments such as liver function, survival and HRQoL rather than liver biopsy.

Previous clinical trials using MSCs across a range of aetiologies of liver disease have yielded mixed results. In trials which reported efficacy, the apparent benefit was transient, with no long-term improvement.^40 41^

One important rationale for using macrophages relates to the lack of efficacy of haematopoetic stem cells,^42^ inherent challenges of using transplanted hepatocytes, and potential risk of introducing transplanted hepatocytes MSCs into a hostile host niche. Previous trials have demonstrated concerns around cellular engraftment and expansive potential of such approaches.

Preclinical studies undertaken by our group have administered macrophages via the portal vein, tail vein or intrasplenic route, but in our phase 1 trial we successfully used peripheral intravenous infusion which is safer and more convenient. While there is no cell-tracking technique used in this trial to assess cell engraftment/durability, animal models and human case reports suggest that macrophages infused via either peripheral or central veins will transiently pass through the lungs, before engrafting in the liver and spleen.^21^ However, hepatic artery or portal venous administration are considerably more invasive, with concerns regarding risk of bleeding and vessel injury,^43^ and problems related to reversal of portal flow/porto-systemic shunting or splanchnic vessel thrombosis.^14^

Through this trial, we aim to add to the collective knowledge of this potential new therapeutic modality for liver disease in this patient population who currently have limited treatment options. If effective, autologous macrophage cell therapy will improve clinical outcomes and enhance HRQoL in people with cirrhosis.

Following initial trial results, we expect that a further extended study will be necessary to determine longer-term safety and the durability of treatment responses. Moreover, it is not yet clear whether patients may require repeat treatments to maximise efficacy.

We hope that this initial phase II trial will provide robust evidence to support and inform future trial design.

## Ethics and dissemination

The trial will be conducted according to the ethical principles of the Declaration of Helsinki 2013 and has been approved by Scotland A Research Ethics Committee (reference 15/SS/0121), NHS Lothian Research and Development department and the MHRA-UK. Good Clinical Practice regulations will be followed and written informed consent will be obtained from all participants. Results will be disseminated through peer-reviewed publications, presented at conferences and published on ClinicalTrials.gov. Ownership of the data arising from this study resides with the study team and their respective employers. The study team will follow the International Committee of Journal Editors guidelines. Requests for data access should be sent to the corresponding author (ORCID: [name]).
